#### 2.6.5. Prescribed Drugs

We will collect information about prescribed drugs throughout the study period. Those drugs will be classified, in principle, into the four categories: antipsychotics, mood stabilizers, antidepressants, and benzodiazepines. Furthermore, the equivalent doses of chlorpromazine, diazepam, and imipramine will be calculated [40].

### 2.7. Data Collection and Data Management

The assessments will be conducted at baseline and 4 weeks after the end of the last stimulation (Table 2). All evaluations will be conducted by experienced psychologists. The data will initially be recorded in a paper file and each participant will be assigned a code number. These files will be stored in a locked security box. After the follow-up data are collected, all data in the paper files will be transcribed to the Electronic Data Capture system (HOPE eACReSS; Fujitsu, Tokyo, Japan), which is a secure system designed for storage of personal and patient data. The data will be sent to independent data managers to assess whether the data are collected properly, focusing on the status of consent acquisition, eligibility of participants, evaluation items, and confirmation of drop-out/terminated cases. These data managers will also oversee and review the progress of the trial. If a participant withdraws their consent, they will be dismissed from the study. At the same time, we will record the dropout rate, and the number of people with adverse events requiring treatment. We will define a dropout rate of less than 10% as a safety criterion and perform a quantitative assessment of safety. The Efficacy and Safety Assessment Committee, whose members are independent of the research and come from the National Center of Neurology and Psychiatry, will check and assess whether the trial is conducted safely and properly, and will also decide whether to stop the trial if any severe adverse events or protocol violations occur. In addition, an on-site data monitor will conduct monitoring to ensure the trial is performed properly, data is properly recorded, and data reliability is ensured. If we conduct any necessary protocol modifications, we will report them to the Clinical Research Review Board, and to the Ministry of Health, Labor and Welfare for registration in the Japan Registry of Clinical Trials website (https://jrct.niph.go.jp).

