## 2. Study Protocol

### 2.1. Trial Design

This study investigates the efficacy and safety of multi-session tDCS over the left STS to improve social cognition for patients with schizophrenia. This is a single-center trial at National Center of Neurology and Psychiatry, Tokyo, Japan. An open-label, single-arm study will be conducted on 15 participants with a diagnosis of schizophrenia based on the Diagnostic and Statistical Manual of Mental Disorders (DSM-5). We selected an open-label, single-arm design, because there is no precedent for tDCS over the left STS, and the major focus of this study is to verify the tolerability and safety of tDCS over the STS. Participants will receive 10 sessions of active tDCS in 5 consecutive days (twice per day) (see Figure 1). The study design is in accordance with the 2013 Standard Protocol Items: Recommendations for Interventional Trials (SPIRIT) Statement (Table S1) [28]. This study was registered within the Japan Registry of Clinical Trials (Trial ID: jRCTs032180026).

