### 2.4. Sample Size Calculation

Total study sample sizes of *n* = 15 have been recommended by our previous study [29], assuming an estimated mean UCSD Performance-based Skills Assessment-brief (UPSA-B) difference from baseline to follow-up of 10.6, with a standard deviation of 15.5. Under these conditions, the power of the primary analysis was 0.8, so approximately *n* = 13 was estimated (one-sample Student’s t-test). Therefore, it was decided to include a total of 15 samples, taking into account the dropouts of the study.

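### The end-of-trial safety assessment rests on one numeric criterion, dropout below 10%, which is a poor proxy for harm, is missed if the two patients the sample size can spare are lost, and is too imprecise with 15 patients

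*Protocol article*

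**What the plan says.** Section 2.1 justifies the open-label, single-arm design partly on the ground that "the major focus of this study is to verify the tolerability and safety of tDCS over the STS".

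Section 2.7 then fixes how safety is to be judged in numbers: "We will define a dropout rate of less than 10% as a safety criterion and perform a quantitative assessment of safety". No confidence level or test is attached, and dropout is not restricted to adverse-event or tDCS-related reasons. The nearest text on leaving the study concerns consent: "If a participant withdraws their consent, they will be dismissed from the study". The same section counts patients whose adverse events needed treatment, but sets no criterion for that count.

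Section 2.4 puts the requirement at about 13 patients ("so approximately *n* = 13 was estimated") and continues: "Therefore, it was decided to include a total of 15 samples, taking into account the dropouts of the study". It states no dropout rate.

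Section 2.6.4 grades adverse events by the care they need, has their severity, treatment and association with the intervention recorded, and stops the whole study once two patients have severe adverse events.

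**The concern.** Followed literally, the criterion can give an answer unrelated to harm, in either direction.

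- **Against safety without harm.** Two patients who withdraw consent for reasons unrelated to stimulation put the trial at 2/15 and the criterion is missed.
- **For safety despite harm.** Patients whose adverse events needed treatment, but who return for follow-up, leave the dropout rate at 0%. Even severe adverse events in two patients, enough to stop the study under section 2.6.4, need not breach the criterion if those patients stay and are not counted as dropouts.

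The threshold also sits awkwardly beside section 2.4, and 15 patients give little information about whether a true rate lies above or below 10%. At stake is the safety statement of a first study of this stimulation site. It would be read alongside the efficacy result if a randomised trial is planned, as the abstract foresees.

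**Working it through.** **Inputs.** Threshold: below 10% (section 2.7). Enrolled: 15. Needed: about 13. Mean UPSA-B change 10.6, SD 15.5, power 0.8 (all section 2.4). Alpha and sidedness are not stated; 0.05 is assumed here, and both sidednesses are tried.

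**1. The plan's own figure.** For a one-sample comparison, n = [SD × (z_alpha + z_power) / difference]².

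- One-sided 0.05: [15.5 × (1.645 + 0.842) / 10.6]² = 13.2, which matches about 13. Exact t-test power reaches 80% at n = 15.
- Two-sided 0.05: the formula gives 16.8, so 17, and the exact t-test needs 19.

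The stated 13 is therefore recovered approximately under a one-sided 0.05. The rest takes 13 and 15 as given and does not depend on this step.

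**2. What the sample size can absorb.** 15 − 13 = 2 patients, and 2/15 = 13.3%. This is the most that can be lost while keeping 13; it is not a stated expectation. Rounding up to 15 fits any assumed dropout from just over 1 − 13/14 = 7.1% to 1 − 13/15 = 13.3%. For example, 10% gives 13/0.90 = 14.4, so 15.

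**3. Which results meet the criterion.** 0/15 = 0% and 1/15 = 6.7% meet it. 2/15 = 13.3% does not.

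**4. How often it is met.** With true dropout p, P(at most 1 of 15) = (1 − p)^15 + 15p(1 − p)^14. At p = 0.10 this is 0.206 + 0.343 = 0.549.

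| True dropout | Chance the criterion is met |
|---|---|
| 5% | 82.9% |
| 10% | 54.9% |
| 13.3% | 38.7% |
| 15% | 31.9% |
| 20% | 16.7% |

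So it is met more than half the time at 10%, a rate it is not meant to accept, and missed 17% of the time at 5%.

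**5. Precision.** Exact (Clopper-Pearson) 95% upper limits; for 0/15 the two-sided limit is 1 − 0.025^(1/15).

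| Dropouts | Observed | Upper limit, two-sided | Upper limit, one-sided |
|---|---|---|---|
| 0/15 | 0% | 21.8% | 18.1% |
| 1/15 | 6.7% | 31.9% | 27.9% |
| 2/15 | 13.3% | 40.5% | 36.3% |

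The limit rises with each dropout, so no result in 15 patients puts it below 10%. With zero dropouts that would take 36 patients (two-sided) or 29 (one-sided); with one dropout, 54 or 46.

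**The case against.** The best defence is that the dropout figure was never meant to stand alone. Adverse events are checked around every session and recorded with severity and association. Treated events are counted, an independent committee reviews safety, and the annual and final reports include serious and nonserious events. In a first single-arm study an observed benchmark is a common device, and detail on denominators and intervals may sit in a fuller document. This defence is right that harm data are collected. It does not answer the point that the article itself chooses dropout, without regard to cause, as the numeric criterion for safety. That is a stated rule, not an omitted detail.

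Four stronger readings are tempting, and the documents do not support them.

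- **That this is the trial's only quantitative safety rule.** Section 2.6.4 has a numeric study-stopping rule. Dropout is the only numeric criterion for the end-of-trial assessment.
- **That dropout says nothing about safety.** Some patients may leave because they tolerate tDCS poorly, so it is a poor proxy and not an irrelevant one.
- **That the trial plans for two dropouts and would then declare tDCS unsafe.** Section 2.4 states no rate and is compatible with an expectation below 10%. A recruitment buffer and a benchmark may legitimately differ, and no consequence is attached to missing the benchmark.
- **That the criterion cannot be met with 15 patients.** The protocol sets an observed-rate benchmark, which 0 or 1 dropout meets. The confidence limits bear on what may be inferred about the true rate. Nor is it true that no result can exclude 10%: 5/15 has an exact interval of 11.8% to 61.6%, which lies wholly above it. What no result can do is exclude rates above 10%.

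**Conclusion.** The concern holds in this form: an all-cause dropout rate is a poor basis for the safety conclusion of a trial whose stated major focus is safety, and 15 patients cannot bear the weight placed on the 10% figure. The criterion turns on one patient, being met at 6.7% and missed at 13.3%. It is met 55% of the time at a true dropout of 10%. Even its best possible result leaves dropout rates up to about 22% open.

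This rests on three assumptions: that dropout carries no restriction by cause, as the article reads; that all 15 patients form the denominator; and that dropouts are independent with a common probability. If a fuller document limits dropout to tDCS-related reasons, the criticism that unrelated withdrawals count against safety falls away. Treated patients who complete would still be missed, and the precision argument would stand. Eligibility, data collection and the primary efficacy analysis are not affected.

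**What to change.** - Base the safety conclusion on three proportions among all patients who received at least one session: those with an adverse event that needed treatment, those with a serious adverse event, and those in whom tDCS was stopped because of an adverse event. Give each an exact 95% confidence interval.
- Relabel the dropout rate as retention or tolerability, and report it by reason.
- State in advance what 15 patients can show: 0/15 only excludes rates above about 22% (two-sided 95%).
- Reconcile the 10% figure in section 2.7 with the dropout allowance in section 2.4. State the dropout rate assumed there, and say whether losing two patients is within plan.

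The cost is wording and a small table. Sections 2.6.4 and 2.7 already have severity, treatment and association recorded and treated events counted; the reason for each dropout and for each stopping of tDCS should be noted if it is not already. The drawback is a more modest safety claim.

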### 2.8. Statistical Analysis

Correlations between baseline values and their changes from baseline of SCSQ, Hinting Task, FEST, BACS, UPSA-B, and PANSS scores, will be evaluated. Correlations will be examined for chlorpromazine equivalent dose of antipsychotics vs. changes from baseline of SCSQ, Hinting Task, FEST, BACS, UPSA-B, and PANSS scores. Correlations will also be examined for the change of UPSA-B scores from baseline and changes of the corresponding scores from baseline.

Statistical analysis will be conducted using STATA 14, created by StataCorp in TX, USA. For continuous variables in the SCSQ, Hinting Task, FEST, BACS, UPSA-B, and PANSS, we will use Student’s t-test. Pearson’s product moment correlation coefficient will be used for the relationship between clinical variables.

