### 2.3. Inclusion and Exclusion Criteria

Participants must meet the following inclusion criteria:(1)Diagnosed as schizophrenia in DSM-5.(2)Aged between 20 and 70.(3)Being able to understand the objectives and content of the study, and provide consent to participate in it. (The ability to consent to participate in this study will be considered insufficient, when patients’ Intelligence Quotient (IQ) is less than 70, or they present with acute psychiatric symptoms. Those patients will be provided with necessary medical care separately from this trial.)(4)Having Social Cognition Screening Questionnaire (SCSQ) scores of less than 34 points. Therefore, participants whose scores are 34 or more will be excluded from this study.

Patients with any of the following conditions will be excluded from the study:(1)Present or past history of severe organic lesions in the brain, dementia, or epilepsy.(2)With alcohol or substance use disorder that was present within 12 months from screening.(3)Contraindicated against electro convulsive therapy or tDCS, e.g., severe cardiovascular diseases, such as myocardial infarction, or aneurysms at high risk of rupture.(4)Were treated with tDCS or other neuromodulations within the past 2 months. (We will ask whether participants have any history of tDCS or other neuromodulations.)(5)Deemed inappropriate to participate judged by the principal investigator, e.g., when participants’ psychiatric symptoms are unstable.

The dose of psychotropic drugs will not be changed during the study period. Cognitive rehabilitation will not be performed during the period. Therefore, we will exclude patients who are scheduled for cognitive rehabilitation.

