### 2.6. Outcomes

Patients receive a psychological evaluation, including a screening evaluation, after being briefed on the purpose of the study and agreeing to participate in the study. Psychological assessment data will be collected at baseline and 4 weeks after the final stimulus (see Table 2). Baseline and follow-up evaluations will be performed by experienced psychologists who are not blinded. Although the interval between the baseline and follow-up evaluation is more than 5 weeks, which secures adequate washout period, the leaning effect of psychological evaluation will be a possible limitation.

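### Correlating each baseline score with its own change builds in a tendency to negative correlation, so zero is the wrong reference value even if tDCS has no effect

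*Protocol article*

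**What the plan says.** The first analysis listed in section 2.8 is: "Correlations between baseline values and their changes from baseline of SCSQ, Hinting Task, FEST, BACS, UPSA-B, and PANSS scores, will be evaluated". The natural reading is that each score's baseline is set against that same score's change. The method follows in the same section: "Pearson’s product moment correlation coefficient will be used for the relationship between clinical variables".

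Three other parts of the protocol bear on this:

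- Section 2.1 fixes the design: "An open-label, single-arm study will be conducted on 15 participants with a diagnosis of schizophrenia". There is no control group.
- Section 2.6 allows one measurement before and one after treatment: "Psychological assessment data will be collected at baseline and 4 weeks after the final stimulus". It names a learning effect as a possible limitation, but not regression to the mean.
- Section 2.3 selects patients on the primary outcome itself: "Having Social Cognition Screening Questionnaire (SCSQ) scores of less than 34 points".

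The text gives no reference value other than zero for these correlations and no correction for the shared baseline term.

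**The concern.** Write X for baseline and Y for follow-up. The planned correlation is between X and Y - X. A patient whose baseline is low by chance has a low X and, for the same reason, a high Y - X. The two variables are therefore negatively related before any treatment effect is considered, and a correlation of zero does not represent no effect.

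What is at stake is the reading of the result. A negative correlation would look as if more impaired patients gained more from stimulation. On a scale where high is good, low scorers appear to rise. On PANSS, where high is worse, high scorers appear to fall. Several scales showing the same pattern could look like replication when all share one artefact. Without a control arm, the trial itself has nothing to show how much of the pattern would have arisen without stimulation.

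**Working it through.** **The plan's own figure.** Section 2.4 assumes a UPSA-B "difference from baseline to follow-up of 10.6, with a standard deviation of 15.5" and reports that "the power of the primary analysis was 0.8, so approximately *n* = 13 was estimated (one-sample Student’s t-test"). With a one-sided alpha of 0.05 (assumed; none is stated) and the normal approximation, n = ((1.645 + 0.842) × 15.5 / 10.6)² = 13.2, which agrees. This calculation does not bear on the present point, except that its SD of change is used in step 3.

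**1. Expected correlation under no effect.** Let rho be the retest correlation and k the ratio of follow-up SD to baseline SD. Then

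corr(X, Y - X) = (rho·k - 1) / sqrt(1 + k² - 2·rho·k).

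With k = 1 this reduces to -sqrt((1 - rho)/2). Neither rho nor k is in the protocol; both are assumptions. Equal SDs (k = 1) is the natural case if treatment does nothing.

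**2. False significant negatives for unselected scales.** Simulated trials with n = 15, no effect, k = 1, and a two-sided 5% test of r against zero (critical |r| = 0.514):

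| Assumed rho | Expected r | r below zero | Significant negative (nominal 2.5%) |
|---|---|---|---|
| 0.5 | -0.50 | 98% | 50% |
| 0.7 | -0.39 | 93% | 31% |
| 0.9 | -0.22 | 80% | 12% |

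With 13 patients, the share significant in either direction is 43%, 26% and 12%, against a nominal 5%.

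**3. UPSA-B, using the protocol's SD of change.** With equal SD s at both visits, the expected r is -15.5/(2s). The value of s is not given. For an assumed s of 15, 18 and 20 the result is -0.52, -0.43 and -0.39.

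**4. SCSQ, allowing for the entry cut.** Where a score of 34 falls in the baseline distribution is not stated, so three positions were tried. Entries are the rates of false significant negatives at n = 15:

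| Assumed rho | Cut 0.5 SD below mean | Cut at mean | Cut 1 SD above mean |
|---|---|---|---|
| 0.5 | 18% | 23% | 35% |
| 0.7 | 11% | 14% | 21% |
| 0.9 | 6% | 7% | 9% |

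The expected r is about -0.12 to -0.42 across these cases. Truncation weakens the artefact but does not remove it.

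**5. The alternative.** Oldham's method correlates Y - X with (X + Y)/2. The covariance is (Var Y - Var X)/2, which is zero when the variances are equal. This is the Pitman-Morgan comparison.

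- Unselected scales, no effect, k = 1: mean r is 0.00 and 5% of tests reject, at every rho tried.
- SCSQ: the cut shrinks Var X more than Var Y, so Oldham's r is pushed upwards, to about +0.10 to +0.52 with the cut between 0.5 SD below and 1 SD above the mean. With the cut at the mean and rho = 0.7 it averages +0.35 and rejects in 28% of trials.
- Response varying between patients independently of baseline, with SD 0.7 of the baseline SD: Var Y rises by 0.49. At rho = 0.7, r = 0.245 / sqrt(1.09 × 0.9725) = +0.24. Simulated over rho 0.5 to 0.9, mean r is about +0.20 to +0.28, with 12% to 18% rejection.

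**The case against.** The strongest reply is that this is a supporting analysis in a 15-patient open-label trial whose stated major focus is tolerability and safety. Section 2.8 only says the correlations will be evaluated. It states no hypothesis of differential benefit, no alpha for them and no decision rule. That is correct: the test against zero is inferred from usual practice with Pearson's coefficient. It limits the weight of the point but does not remove it, because even a purely descriptive r is naturally read against zero.

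A reader might infer four stronger things that the protocol does not support:

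- **That a negative correlation is bound to appear.** It is an expectation. Under no effect, 2% to 20% of trials of 15 give r at or above zero for rho 0.5 to 0.9. The sign can reverse if follow-up SD is clearly larger: k = 1.2 with rho = 0.9 gives +0.15.
- **That the 50%, 31% and 12% rates hold for all six scales.** They assume no selection on baseline. Section 2.3 selects on SCSQ, so the lower rates in step 4 apply there.
- **That the artefact would shape eligibility for a later randomised trial.** The Abstract ties that trial to whether social cognition improves, and nothing links it to these correlations.
- **That the efficacy tests are compromised.** The coupling does not touch the t-tests of change.

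A further fair objection is that Oldham's method is not a clean answer. It tests variances and can drift positive when response varies between patients. That stands, and the limit has to be written into the plan. Omitting the correlations, or reporting them descriptively with a caveat, would also be defensible.

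**Conclusion.** The point holds as a defect in a stated, supporting analysis. As written, section 2.8 plans correlations that tend to be negative when treatment does nothing, and nothing in the text corrects for it. The inflation is large for the five unselected scales and smaller, but still above the nominal 2.5%, for SCSQ.

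The sizes rest on assumed retest correlations of 0.5 to 0.9, equal SDs at the two visits, normally distributed scores and, for SCSQ, an assumed position of the cut. The direction for unselected scales requires only rho·k below 1. The change should be made, but no primary conclusion depends on it.

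**What to change.** Replace the first sentence of section 2.8 along these lines:

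> *For the Hinting Task, FEST, BACS, UPSA-B and PANSS, change will be correlated with the mean of the baseline and follow-up values (Oldham's method, equivalent to the Pitman-Morgan test). This tests equality of the variances at the two visits. A positive value can arise if response varies between patients independently of baseline. No such correlation will be calculated for SCSQ, because patients are selected on its baseline value. No conclusion that more impaired patients benefit more will be drawn from a raw correlation of baseline with change.*

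Using Oldham's method for the other five scales assumes that their measurement errors are independent of the SCSQ error at baseline. Under that assumption, with these scales correlated 0.3 to 0.5 with SCSQ and SCSQ cut at its median, a simulation gave a mean Oldham r of 0.00 and 5% rejection.

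The cost is a short text amendment. It needs no new data, visits or patients.

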## 3. Ethics Statement

The study will be performed according to the Declaration of Helsinki and will follow the Clinical Trials Act in Japan. The protocol has been presented for approval by the National Center of Neurology and Psychiatry Clinical Research Review Board (CRB3180006). The principal investigator (TS) will have the ultimate responsibility for providing informed consent to all research participants. All participants must agree to participate in the study. After initial review and approval (September 2018), the institution’s clinical research review committee will review the protocol and implementation at least annually. Two annual reviews have proceeded to date (https://jrct.niph.go.jp/re/bulletins/detail/312/22, https://jrct.niph.go.jp/re/bulletins/detail/312/1540). The principal investigator should submit a safety and progress report to the Review Board at least annually, and the researcher should submit the final report within 3 months of the completion of the study. These reports will include a summary of the total number of enrolled participants, serious/nonserious adverse events that occurred, and safety and monitoring committee reviews [41]. Changes related to the research protocol need to be submitted to the Clinical Research Review Board for review as a protocol modification. If a participant needs to be treated due to a moderate or severe adverse event directly caused by tDCS, the participant will receive the full cost of treatment from clinical trial insurance.

